This study is based on the concept that therapeutically effective processes are common to all arts therapies modalities [1, 15–20]. Accordingly, NICE combines the evidence for them in one analysis [21]. However, for any arts therapy to have an effect, patients need to engage with the group and the art form used. The appeal of art forms and patient preferences vary. A poor match of preference and the offered art form is likely to lead to poorer attendance and—even in attending patients—poorer outcomes, as suggested by both MATISSE and NESS trials [9, 10]. A similar picture is seen in wider psychological treatment, preference matching is associated with lower dropout and higher therapeutic alliance [22], whereas lack of preference matching has been associated with lower perceived benefit from treatment [23–25]. Also, it does not really reflect the clinical reality as patients, if they have a choice, rarely accept a form of arts therapy that does not strongly appeal to them.

We will test whether arts therapies provided in groups are effective for diagnostically heterogeneous patients in mental health services. Patients will choose which of the three forms of arts therapy they want to participate in, thus providing modality ‘preference strata’ within which patients will be randomised to either their preferred form of arts therapy or an active group counselling control. They will be offered 40 sessions over a 5-month period. Outcomes will be assessed at baseline, at the end of treatment, and after 6- and 12-month post-intervention follow-up periods. Overall, the study will provide pragmatic evidence for the effectiveness and cost-effectiveness of group arts therapies as they are most commonly provided within NHS community mental health services.

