## Assignment of interventions: allocation

### Sequence generation {16a}

Randomisation will be on a site-by-site basis (three sites in the first phase of recruitment, and four sites in the second stage) and will be further stratified at each site by preferred modality. To minimise the time between enrolment and commencing the intervention, we will aim to conduct randomisation as soon as a batch of 20 people with the same modality preference have been enrolled at a site and have completed baseline measures. Participants in each batch of 20 will be randomised in a 1:1 ratio to two therapy groups, one receiving the preferred modality and one receiving group counselling (the control), using constrained randomisation to balance the distribution of primary diagnosis, age and gender in each therapy group. We implement constrained randomisation using the cvrand command in Stata [42].

If 15–19 participants with a preferred modality are still to be randomised at the end of the recruitment window, they will be randomised 1:1 to two therapy groups, with the possibility to add non-study participants to maintain numbers within the group. In the case where there are fewer than 15 participants with a preferred modality at the end of the recruitment window, they will be randomised (where feasible) in a 2:1 ratio to intervention and control, with the option of enlarging groups with non-study patients.

At the end of recruitment, there is a chance that the number of participants with a preferred modality is below that of the number required to feasibly run a group. Taking into account drop-out and non-attendance, we estimate that we require a minimum of 8 participants for a group to be viable. This equates to a minimum of 12 participants in a randomisation batch if randomising 2:1. In order to minimise the loss of already consented participants, we will ask participants to provide a second modality choice and also to indicate whether or not they would be willing to receive this in case numbers for their original preferred modality cannot be met.

Where the number in a preference stratum at the end of recruitment is fewer than 12, we will consider enriching this stratum with participants for whom the modality was their second choice, to give a sufficient number to be randomised as a batch. If a participant is unwilling to receive a second choice, we will withdraw them from the study and signpost them to local services.

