**Primary outcome analysis**

The primary analysis will be a longitudinal mixed regression analysis that includes end of treatment, 6-month post-treatment and 12-month post-treatment assessments of psychological distress, using all non-missing data on these outcomes. Performing a longitudinal analysis of all time-points using all non-missing data should allow for greater precision in the estimation of treatment effect at end of treatment than an analysis of this time-point alone. However, to allow results on the primary outcome to be reported in a timely fashion, we will also conduct and report an initial analysis of the first two time-points—baseline and end of treatment—as soon as these are available for all participants. The analysis will include random effects to allow for clustering within each therapy group and individual. The primary hypothesis of a beneficial effect of arts therapy will be investigated by testing for a fixed effect of intervention vs. control, adjusting for fixed effects of site, patients’ preference for the form of arts therapy (art, music or dance), primary diagnosis, age, sex and baseline psychological distress. The primary analysis will be by intention to treat. Secondary analyses will investigate the treatment effect in compliers.

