### Methods for additional analyses (e.g. subgroup analyses) {20b}

**Subgroup analyses**

We will repeat analyses within diagnostic subgroups and investigate whether different forms of arts therapy have different effects by including an interaction between modality preference stratum and intervention vs. control in our mixed regression model.

Qualitative assessments and nested process evaluation

We plan to conduct a process evaluation in line with recommendations by the Medical Research Council [49]. The logic model of our intervention (described in our manual development paper [28]) provides a theory of the intervention describing assumptions and contextual factors that might shape implementation and outcomes, hypothesised processes and mechanisms of impact and our intended outcomes. The aim is to better understand the processes of group arts therapy in comparison to group counselling controls in practice and possible implications. In particular:

To understand exactly how the intervention was delivered in practice (treatment fidelity analysis).Describe processes of attendance and hypothesised process factors of self-reported depression, group experiences and session appraisal over the course of the trial.Understand subjective experiences and attributions for change of the intervention from the perspective of patients and arts therapists.Compare reported quantitative and qualitative processes against the proposed logic model and to revise accordingly.

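### The preference-stratum-by-arm interaction is said to test whether forms of arts therapy differ in effect, but it compares self-selected groups of patients and cannot support that inference

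*Protocol article*

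**What the plan says.** All references are to the protocol article.

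- **Subgroup analyses {20b}:** the plan will "investigate whether different forms of arts therapy have different effects by including an interaction between modality preference stratum and intervention vs. control" in the mixed regression model. The question is about forms of therapy; the model term is about preference strata.
- **Background and rationale {6a}:** "Patients will choose which of the three forms of arts therapy they want to participate in". Within the resulting strata they are "randomised to either their preferred form of arts therapy or an active group counselling control".
- **Sequence generation {16a}:** randomisation is by site and "will be further stratified at each site by preferred modality". Each batch is split between one arts group and one counselling group, "using constrained randomisation to balance the distribution of primary diagnosis, age and gender in each therapy group". A stratum with fewer than 12 patients at the end of recruitment may be topped up with patients for whom that form was their second choice.
- **Primary outcome analysis {20a}:** the model adjusts for site, preferred form, "primary diagnosis, age, sex and baseline psychological distress", all as fixed effects. No covariate-by-arm term is stated.
- **Objectives {7}:** type of arts therapy and diagnosis are listed among the questions to be explored in subgroup analyses.

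**The concern.** The stated question is whether art, dance movement and music therapy have equal effects. The null hypothesis of the interaction is different: that the effect of the preferred form against counselling is the same in three groups of patients who sorted themselves. Apart from possible second-choice enrichment, form and patient group coincide completely in the intervention arm, so no contrast in the trial compares two forms in the same kind of patient.

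Suppose a characteristic that changes the benefit of any arts group over counselling is more common among those who choose one form. The interaction is then non-zero although the forms are equivalent for each patient. A difference between strata in the response to counselling has the same consequence. In the other direction, patient mix can cancel a real difference between forms. If the result is read as the text invites, it could influence which therapies services provide. The planned cost-effectiveness ratio for each form (Economic evaluation, sensitivity analysis 6) would stand beside it and needs the same caution.

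**Working it through.** **1. What the design identifies.** Let Δk be the effect of arm in preference stratum k. Arm is randomised within stratum, so each Δk is estimated without confounding. If, for a given patient, every form has the same effect, which depends on a binary trait x, then

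Δk = e0 + (e1 − e0) × pk,

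where e0 and e1 are the effects without and with the trait and pk is its share in stratum k. The Δk differ whenever e1 ≠ e0 and the pk differ, although form has no role. A main effect of x shifts outcome levels in both arms equally and leaves e1 − e0 in the interaction. Constrained randomisation balances diagnosis, age and gender between the two groups of a batch, not across strata.

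**2. The plan's own sample size, as a check on inputs** (Sample size {14}: 0.5 SD, ICC 0.1, 8.5 analysed per cluster, CV 0.5, 15% drop-out, 90% power, 5% taken as two-sided).

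- Unclustered n per arm = 2 × ((1.960 + 1.282)/0.5)² = 84.06.
- Design effect = 1 + ((1 + 0.5²) × 8.5 − 1) × 0.1 = 1.9625.
- Per arm before drop-out = 84.06 × 1.9625 / 0.85 = 194.1, or 19.4 clusters. Rounded up to 20 clusters this is 200, as stated.

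The plan gives no figure for the interaction.

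**3. Precision of the between-stratum contrast.** Assume three equal strata and 1:1 allocation.

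- Analysed: 420 × 0.85 = 357, or 119 per stratum and 59.5 per arm within stratum.
- Variance of one stratum effect (SD units) = 2 × 1.9625 / 59.5 = 0.0660; SE 0.257.
- SE of a difference between two strata = √2 × 0.257 = 0.363.
- Power for 0.5 SD: 0.5/0.363 = 1.377, which gives 28%.

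The article cites a group body psychotherapy trial whose ICC did not exceed 0.01; the design effect is then 1 + 9.625 × 0.01 = 1.096. For baseline adjustment, assume that baseline explains 40% of the variance (variance × 0.6); the documents give no such figure.

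| ICC | Baseline adjustment | SE of difference | Power for 0.5 SD |
|---|---|---|---|
| 0.1 | none | 0.363 | 28% |
| 0.1 | 40% of variance | 0.281 | 43% |
| 0.01 | none | 0.271 | 45% |
| 0.01 | 40% of variance | 0.210 | 66% |

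**4. How often the interaction rejects when the forms are equivalent.** The test is a 2-df Wald test at 5%, with noncentrality Σ(Δk − mean Δ)² / 0.0660. The trait shares and the difference e1 − e0 are assumptions. ICC is 0.1, without baseline adjustment.

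| Trait shares in the three strata | e1 − e0 = 0.5 SD | 0.75 SD | 1.0 SD |
|---|---|---|---|
| Equal shares | 5.0% | 5.0% | 5.0% |
| 60/50/40% | 5.6% | 6.3% | 7.4% |
| 70/50/30% | 7.4% | 10.5% | 15.2% |
| 85/50/25% | 10.5% | 18.3% | 29.8% |

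Example, 70/50/30% and 1.0 SD: the stratum effects lie 0.2 above, at, and 0.2 below their mean; 0.08/0.0660 = 1.21, so rejection is 15.2%. With the assumed baseline adjustment the last three rows become 6.0–9.0%, 9.0–22.8% and 14.6–46.8%.

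**5. Simulation** (1,500 clustered trials per setting). With the trait as a main effect only, shares of 70/50/30% and a 1.0 SD difference gave 14.7% rejection (15.2% by formula), and shares of 80/50/20% gave 30.1% (29.5% by formula). Adding the trait-by-arm term brought rejection back to about 4–6% in all settings. This works only for a trait that is measured and in the model.

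**The case against.** The strongest reply is that the analysis is exploratory, names the preference stratum openly and carries no decision rule. It also suits a pragmatic trial: the authors hold that patients rarely accept a form that does not appeal to them, so whether the effect differs between forms as delivered to those who choose them is a fair question. Most of this stands. It limits the weight of the point and shows that the analysis is worth keeping under the right description. It does not make the term a comparison of forms, which is what the sentence says it investigates.

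The size is also open to challenge, rightly. The documents give no stratum composition, no effect modifier and no link between preference and diagnosis. Modifier differences of 0.5 to 1.0 SD equal or double the whole design effect. With shares of 60/50/40% the excess is small.

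Three stronger readings are tempting, and the documents do not support them:

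- **That the test has an inflated type I error.** If the stratum effects truly differ, the interaction null is false and rejection is correct. The error lies in the conclusion drawn about forms.
- **That the plan expects the effect to vary by diagnosis.** It only explores diagnostic subgroups.
- **That a modality difference could be called supported if it persists after arm-by-covariate terms are added.** Such terms deal only with measured modifiers, so persistence would not identify an effect of form.

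Finally, covariate-by-arm sensitivity models are commonly left to the SAP, which is not shown. Their absence is no fault; the fault is the inference that the article does state.

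**Conclusion.** Wrong as written, in the stated inference of an exploratory analysis; the primary analysis is unaffected. The structural point needs no assumed numbers: form is chosen, only arm is randomised within stratum, and main-effect adjustment leaves differences in the arm effect untouched.

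The practical size is unknown. The illustrated range of about 6% to 30% rejection with equivalent forms (ICC 0.1, no baseline adjustment) rests entirely on assumed trait shares and modifier effects. It falls to 5% if no effect modifier is unevenly spread across strata. A non-significant result is weak evidence too: power for a 0.5 SD difference between two forms is 28% or 43% at ICC 0.1 and 45% or 66% at ICC 0.01, without and with the assumed baseline adjustment, for three equal strata and 1:1 allocation. A reader might infer from the article that a significant interaction would show one form to be better, or that a non-significant one would show the forms to be equal. The design supports neither.

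**What to change.** In Subgroup analyses {20b}:

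1. Define this exploratory analysis as whether the effect of being offered one's preferred arts group, compared with counselling, differs between preference strata.
2. Report the three within-stratum effects with 95% CIs.
3. State that a significant interaction will not be read as showing that the forms differ in effectiveness, nor a non-significant one as showing that they are equal.
4. As a sensitivity analysis only, refit the model with arm-by-diagnosis, arm-by-sex, arm-by-age and arm-by-baseline-GSI terms, to show how far measured patient differences account for any heterogeneity. Attach no rule that persistence supports a modality difference.

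The cost is a few sentences and one further model on data already collected. The price is a weaker statement about modality and a less precise interaction estimate in the adjusted model.

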**Method**

The process evaluation will employ an embedded mixed methods design and will consist of data collection of video data of the intervention itself (through treatment fidelity analysis), client self-reported measures (weeks 2, 7, 12, 17 PHQ9, FE-GES, ORS) and qualitative end interviews scheduled within 6 months of the end of the intervention with participants and arts therapists. The interview is optional for participants but we aim to conduct a minimum of 45 interviews.

Quantitative analysis will provide a descriptive analysis of the course of process measures. We will descriptively explore whether there are any differences between compliant and non-compliant attenders, responders and non-responders and whether any socio-demographic and clinical characteristics are associated with outcomes.

Qualitative evaluation will comprise of one-off end-of-study interviews with participants from all 3 arts therapies modalities and control groups within 6 months of the intervention ending (weeks 20–48).

Participants will be purposively sampled so that we have a range of characteristics based on the following: treatment completers (attended > 75% of sessions) and partial-attendance (attended 35–75% of sessions), representation of each of the diagnostic groups (ICD10 F2, F3, F4), representation of a range of ages, each mode of therapy and sites. We aim to conduct interviews with up to 3 patients per arts therapies group and up to 10 control group participants, with an anticipated sample size of around 55 participants.

Interviews will last up to 1 h and will be conducted by an unblinded member of the research team. We will use an amended version of the Client Change Interview [36], which explores experiences of therapy, changes over a given time period and attributions for this. The amended version used in existing music therapy studies also explores participants’ experiences of the research process and involvement in the study as a whole. This information will provide understanding not only of the interventions but of how best to involve this patient group in trials in the future. Following advice from our LEAP, we will also interview the arts therapists providing the intervention as a means of triangulating patients’ experiences of change and relating identified changes to observations within the sessions. These interviews will also last for 1 h and will happen within 6 months of the therapy group ending.

Given the relatively large qualitative sample size due to nesting of participants within groups and diagnoses, we will initially analyse the material using the framework approach outlined by Ritchie et al. [50] whereby after familiarisation with transcripts, a thematic framework is constructed—informed by the theoretical model for this study and interview content—and then use charting within thematic matrices to examine similarities and differences on core characteristics outlined above across and within themes. We will relate this to the hypothesised theory of the intervention [28] and highlight where our data supports of conflicts with this hypothesis.

### Methods in analysis to handle protocol non-adherence and any statistical methods to handle missing data {20c}

A longitudinal regression analysis of all non-missing data will give a valid estimate of treatment effect under an assumption that outcomes are ‘missing at random’ (that is, missingness is influenced only by variables that are included in the analysis). If the primary outcome is missing for more than 5% of participants, we will conduct further analyses to investigate the sensitivity of our conclusions to departures from the missing at random assumption.

### Plans to give access to the full protocol, participant-level data and statistical code {31c}

The full protocol is available to access from the authors. Once the main findings are published, the full anonymised participant-level dataset will be made available on request.

## Oversight and monitoring

### Composition of the coordinating centre and trial steering committee {5d}

The trial has four management committees: the Trial Management Group (TMG), the independent Trial Steering Committee (TSC), the Data Monitoring and Ethics Committee (DMEC) and the Lived Experience Advisory Panel (LEAP). The TMG includes the CI, co-CI, a range of clinical co-applicants, the main researchers and patient representatives from the LEAP. The TMG will meet regularly (at least every 2–3 months) to ensure all practical details of the trial are progressing and working well, and to ensure everyone within the trial understands them. More regular and individual meetings between the PIs, site leads and different parts of the research team will be arranged as appropriate. The TSC includes an independent chair, clinician, statistician and patient representative. The TSC will meet jointly with the DMEC at the beginning of the study and then immediately following the delivery of expected major milestones. Further meetings will be arranged as and when required. The LEAP will consist up to eight patient and carer members with experience in secondary mental health services or caring for someone accessing such services. They will meet at least twice per year to advise on study materials, progress and findings including website content and development, recruitment strategy, patient-facing information, issues during the running of the trial and contribution towards analysis and interpretations of findings, including suggestions as to how to present these to wider members of the public and develop lay summaries.

### Composition of the data monitoring committee, its role and reporting structure {21a}

The DMEC will include committee members who are completely uninvolved in the running of the trial, independent from the Sponsor, and who cannot be unfairly influenced (either directly or indirectly) by people or institutions involved in the trial. The committee will include one trial methodologist, a statistician and a patient representative. They will meet immediately prior to TSC meetings (and more regularly if required).

### Adverse event reporting and harms {22}

**Adverse events (AE)**

Adverse events will be recorded in the main trial database and the participant’s clinical record, with the participant followed up by the research team.

**Serious adverse event (SAE)**

SAEs will be recorded as above, with the additional completion of serious incident form of the NHS Trust, and notification of the Sponsor within 24 h of research staff becoming aware of the event. Those that are assessed as ‘related’ and ‘unexpected’ will be reported also to the Research Ethics Committee (REC) within required expedited reporting timescales. All deaths will be reported to the Sponsor irrespective of whether the death is related to disease progression, the intervention, or an unrelated event within 24 h of the death becoming known by the research team.

**Urgent safety measures**

If any urgent safety measures are taken, the CI/Sponsor will give written notice to the REC within 3 days of the measures taken and the circumstances giving rise to those measures.

**Overview of safety reporting responsibilities**

The PIs will ensure that local safety monitoring and reporting are conducted according to the Sponsor’s requirements. The CI holds clinical oversight of the safety of patients participating in the trial. The Trial Manager is responsible for reporting all AEs and SAEs to the DMEC on an at least 3 monthly basis. The DMEC and TSC are responsible for periodically reviewing safety data and liaising regarding safety issues.

